### **7.3 Study procedures**

#### **Invitation and enrolment**

Based on live birth data from the CBS (<http://www.cbs.nl/nl-NL/menu/home/default.htm>) the optimal region for the study is assessed. The region will comprise of parts of Utrecht and Noord-Holland and part of Flevoland and Gelderland for group 2. The RIVM-RCP (who send invites for the National vaccination program) uses the region to make an address list and sends this list to the distributor who sends the invites. Invites containing the information leaflet, return card and envelop and a short recommendation letter from the RCP will be send to all addresses on the list.

The parents send in the return card, to show their interest in the study. In response an email will be send with the extra information (including the informed consent form and the general patient brochure from the CCMO).

A telephone call will be made to the parent, to inquire if they are still interested, explain the study in case of questions and to make an appointment. Their address will be registered for the home visit and to send the extra information also on paper.

#### **Inclusion**

Inclusion criteria will be checked during the first home visit, according to the criteria in paragraph 4.2 and 4.3

**Randomization, see paragraph 7.2**

#### **Questionnaire**

The study parameters in the questionnaire are as mentioned in paragraph 7.1.3. The questionnaire is part of the CRF and will be completed by the investigator.

### **Blood sample**

In case of partial or complete failure a second attempt may be performed with consent of the parents. The maximum number of blood collection attempts is 2.

In case of resistance by the child the behaviour code of the Dutch Society of Pediatricians will be followed.

For cellular immunity, an 8 ml blood sample is expected to yield  $8-10 \times 10^6$  PBMC.

$6 \times 10^6$  PBMC are minimally required for culturing and analysis in duplicate wells of memory B cells specific for the selected polysaccharides included in the vaccines and controls. 8 ml blood samples will be collected in 2x 4 ml CPT tubes with sodium citrate (Becton Dickinson, San Diego, California, USA).

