### 3. STUDY DESIGN

Children eligible to receiving the regular vaccinations of the NIP, born after August 2011 (assuring that all children are eligible for and will receive Hepatitis B vaccination)

A controlled, randomized, intervention trial with 2 groups (see figure 2 and table 1).

- Children of group 1 will be invited first (around the age of 1 month), since they have to receive all DTaP-IPV-Hib-HepB and PCV13 vaccinations as part of the trial
  - Vaccinations will be given during home visits
  - Children will be randomized over 2 sub groups in order to diminish the burden of the 8 ml blood sample (which is collected just before or 7-9 days after the 11-months vaccination)
  - For the immune memory, collect 33 children per sub group in order to have 25 evaluable children per sub group (sub group 1a and 1b)
  
- Children of group 2 will be invited around the age of 3.5 months, as to include them in the trial at the age of 5 months
  - Vaccinations are not part of the trial, since they already receive them during well-baby clinic visits
  - Children will be randomized over 2 sub groups in order to diminish the burden of the 8 ml blood sample (which is collected just before or 7-9 days after the 11-months vaccination)
  - For the immune memory, collect 33 children per sub group in order to have 25 evaluable children per sub group (sub group 2a and 2b)

Randomization will be done within group 1 and separately within group 2.

The randomization will not be done for the total study (group 1 and 2 together) since children of the PCV10 group already receive all proper vaccinations in the NIP and randomization would result in a long period between invitation at 1 month of age and inclusion at 5 months of age for the PCV10 group.

Figure 2 Study schedule

[figure not shown]

Blood samples (8 ml) are used for cellular immunogenicity (and 100 ul, of these samples will be used for humoral immunogenicity). Blood samples (100 ul) are used for humoral immunogenicity.

|                                                                                                                               | Group
1a
(PCV13) | Group
1b
(PCV13) | Group
2a
(PCV10) | Group
2b
(PCV10) |
|-------------------------------------------------------------------------------------------------------------------------------|------------------------|------------------------|------------------------|------------------------|

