| 5 months blood collection (heel/finger stick)
Including check in- exclusion criteria, signing of IC                        |                        |                        | x                      | x                      |
| 8 months blood collection (heel/finger stick)                                                                                 |                        |                        | x                      | x                      |
| Randomization                                                                                                                 |                        |                        | x                      | x                      |
| Pre 11 months blood collection (8 ml) Questionnaire                                                                           |                        |                        | x                      |                        |
| Pre 11 months blood collection (heel/finger stick) Questionnaire                                                              |                        |                        |                        | x                      |
| Pre 11 months blood collection (8 ml) & vaccination (PCV13 and DTaP-IPV-Hib-HepB) Questionnaire                               | x                      |                        |                        |                        |
| Vaccination (PCV13 and DTaP-IPV-Hib-HepB) Questionnaire                                                                       |                        | x                      |                        |                        |
| Post 11 months blood collection (7-9 days) Questionnaire                                                                      |                        | x                      |                        | x                      |
| 12 months blood collection (heel/finger stick)                                                                                | x                      | x                      | x                      | x                      |
| End of study for participants                                                                                                 | x                      | X                      | x                      | x                      |

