### **IgG antibodies**

Blood samples will be transported to the CLB and after centrifugation the serum samples will be stored at -80°C. Later, the samples will be tested for all 13 vaccine pneumococcal polysaccharides and DTaP-Hib using the X-map Luminex technology. Only 100 µl of blood is needed for these analyses.

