### **Preparation of PBMCs**

Specific B cell frequencies will be measured for five to six serotypes.

In the previous KOKKI study the following serotypes were tested: 6B, 14, 19F and 23F. They are present in PCV7, PCV10 and PCV13.

For the current study a selection of the 13 serotypes will be made. Probably 6B and 19F from PCV7, one-two serotypes from the three serotypes added by PCV10, and two serotypes added by PCV13 (probably 6A and 19A). The final selection will be based on the carrier frequencies just before evaluation.

Fresh Peripheral Blood Mononuclear Cells (PBMCs) will be separated from heparinized blood, within 24 hours after collection, by density gradient gel centrifugation in CPT tubes (Becton Dickinson). Cells are washed using PBS + 5% fetal calf serum (FCS; HyClone).

PBMC's were resuspended in AIM-V medium containing 10% FCS and supplemented with penicillin (100 U/ml), streptomycin (100 µg/ml) and L-glutamine (200nM) (Gibco BRL).

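### The protocol gives citrate, heparin and serum for the same 8 ml draw, so secondary pre-booster IgG and kinetics may mix plasma and serum, unequally between vaccine groups

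*Protocol*

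**What the plan says.** Four statements in the protocol describe the large blood sample:

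- Section 7.3, Blood sample: "8 ml blood samples will be collected in 2x 4 ml CPT tubes with sodium citrate". No other container is named for this draw.
- Section 3, below Figure 2: "Blood samples (8 ml) are used for cellular immunogenicity (and 100 ul, of these samples will be used for humoral immunogenicity".
- Section 7.3, IgG antibodies: "after centrifugation the serum samples will be stored at -80°C". This covers all IgG samples. No plasma route and no correction between sample types is given.
- Section 7.3, Preparation of PBMCs: the cells "will be separated from heparinized blood, within 24 hours after collection, by density gradient gel centrifugation in CPT tubes".

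Table 1 sets who gives which sample before the 11-month booster. Subgroup 1a has "Pre 11 months blood collection (8 ml) & vaccination (PCV13 and DTaP-IPV-Hib-HepB) Questionnaire", 2a has "Pre 11 months blood collection (8 ml) Questionnaire" and 2b has "Pre 11 months blood collection (heel/finger stick) Questionnaire". Subgroup 1b is vaccinated without a pre-booster sample. Section 3 describes the 8 ml sample as one "which is collected just before or 7-9 days after the 11-months vaccination", so the post-booster sample in 1b and 2b is the 8 ml draw. The 5- and 8-month samples (group 2 only) and the 12-month samples (all subgroups) are heel or finger sticks.

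Section 7.1.2 lists IgG before and 7–9 days after the booster, and the kinetics, as secondary endpoints. Section 9.2 summarises these time points by GMC and by the proportion above 0.35 µg/ml, and uses each child's serial samples for the kinetics.

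**The concern.** A study nurse or laboratory cannot follow the text as it stands. A tube with anticoagulant gives plasma. If the 100 µl for IgG comes from that tube, the sample is not the serum that the IgG section describes. If it is to be serum, a serum tube is missing. The two statements on the anticoagulant also disagree.

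This matters for the analysis because the 8 ml draw is not spread evenly. Before the booster it supplies all PCV13 samples but only half of the PCV10 samples. Within children, the 2a series changes from stick to 8 ml draw at 11 months and back to stick at 12 months, and the 2b pre-to-post change runs from stick to 8 ml draw. If the two sample types read differently, part of a group difference or of a child's change would come from the tube. A larger sample would not remove that. The fixed 0.35 µg/ml cut-off would also act at a different true concentration in the two sample types.

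**Working it through.** **1. Do the statements fit together?** The tube volume is 2 × 4 ml = 8 ml, which is the whole draw, so nothing is left for a serum tube. Citrate and heparin are two different anticoagulants given for the same CPT blood. Neither fits a serum sample. At least two of the three statements in section 7.3 have to change, or a serum aliquot has to be added.

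**2. Share of planned IgG samples taken from the 8 ml draw** (33 per subgroup, sections 3 and 7.5; sources from Table 1):

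| Time point | PCV13 (group 1) | PCV10 (group 2) |
|---|---|---|
| 5 and 8 months | no sample | 0/66 |
| Pre-booster | 33/33 (1a) | 33/66 (2a yes, 2b stick) |
| 7–9 days post-booster | 33/33 (1b) | 33/33 (2b) |
| 12 months | 0/66 | 0/66 |

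The imbalance between vaccine groups exists only before the booster.

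**3. The plan's own yardstick.** Section 4.4 uses a variance of 0.27 and a difference of 0.30 on the log10 scale, with two-sided alpha 0.05 and 80% power (k ≈ 2.80). Then n = 2k²σ²/δ² = 2 × 2.80² × 0.27 / 0.30² = 47.04, and 47/0.80 = 58.75. The stated 47 and 59 reproduce. They rest on the 12-month samples, all sticks in this trial, so this point leaves them unchanged.

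**4. Possible dilution.** The documents give no additive volume. Assumptions: liquid additive a = 0 to 0.15 ml per ml of blood, and plasma fraction p = 0.60 to 0.67. The loss is a/(p + a).

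| a | Loss (p = 0.67 to 0.60) | log10 shift |
|---|---|---|
| 0 | 0% | 0 |
| 0.05 | 6.9–7.7% | 0.031–0.035 |
| 0.10 | 13.0–14.3% | 0.060–0.067 |
| 0.15 | 18.3–20.0% | 0.088–0.097 |

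**5. What remains between the groups.** In a pooled pre-booster comparison of group 1 with group 2, the share from the 8 ml draw is 100% against 50%. Half the shift remains: at most 0.5 × 0.097 ≈ 0.05 log10. That is about 0.05/0.30 = 17% of the difference the trial is sized for. The standard error of this comparison, with the plan's variance and 33 v 66 children, is √(0.27 × (1/33 + 1/66)) = 0.11. The possible bias is therefore at most about 0.05/0.11 = 0.45 standard errors.

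**6. The cut-off.** At a 20% loss, a reading of 0.35 µg/ml corresponds to 0.35/0.80 = 0.44 µg/ml undiluted. Children between 0.35 and 0.44 would be counted as below. How many there would be cannot be derived from the documents.

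**The case against.** The strongest reply is that the protocol shows a wording conflict and no demonstrated bias. It does not say the citrate is liquid, and with no liquid additive the dilution is zero. The one section on IgG says serum, and section 3 does not say that the 100 µl is taken as plasma from the CPT tube. A laboratory manual could settle how the aliquot is made. Even with dilution, the bias is under half a standard error at one secondary time point. Most of this stands, and it is why the point is minor.

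A reader might go further and infer that liquid citrate puts the values on different scales and that the artefact favours PCV10. The documents do not support this. The form and volume of the additive are not given. The direction would hold only for group 2 against group 1, and section 9.2 sets the antibody analysis up as group 2 against the PCV13 arm of the PIM study. The sample type in PIM is not given. If its 11-month samples were serum, dilution in 2a would lower the PCV10 values instead.

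The reply does not remove the conflict itself. Citrate, heparin and serum cannot all describe this sample. The tube is a collection instruction needed at the visit, and Table 1 does make the sample source unequal before the booster, with no bridging or correction stated.

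**Conclusion.** The plan contradicts itself on the tube and on the IgG matrix of the 8 ml draw. As written it may mix plasma and serum in the secondary pre-booster IgG, in the 2a kinetics, in the 2b pre-to-post change and in the matching 0.35 µg/ml proportions. DTaP-Hib antibodies at those visits share the exposure.

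The post-booster comparison of 1b with 2b uses the 8 ml draw on both sides and is balanced. The 12-month primary humoral endpoint uses sticks throughout this trial and is not affected. The cellular primary endpoint is counted per 10⁶ PBMC (section 9.1), so plasma dilution does not touch it.

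The size is conditional. For an additive of 0–15% of blood volume and a plasma fraction of 0.60–0.67, both assumed, IgG from the 8 ml draw reads 0–20% low (0–0.10 log10), and 0–0.05 log10 remains in a pooled pre-booster comparison of groups 1 and 2. Against the PIM arm the direction is unknown. Severity is minor: secondary endpoints only, and cheap to remove.

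**What to change.** - Reconcile the Blood sample, IgG antibodies and Preparation of PBMCs parts of section 7.3. Name one anticoagulant for the CPT tubes and one matrix for IgG, and name the container for the heel and finger sticks, which the protocol also leaves open.
- At the 8 ml venepuncture, put the 100 µl for IgG into the same type of serum microtube as the sticks, and the rest into the CPT tubes. All IgG is then serum at every time point and in every subgroup.
- Cost: one microtube per child at one visit, no extra puncture, and 0.1 of 8 ml (1.25%) less blood for PBMC. The expected yield of 8–10 × 10⁶ PBMC would become about 7.9–9.9 × 10⁶, still above the stated minimum of 6 × 10⁶.
- If samples already exist, record the matrix of each one. Before the booster compare like with like (1a v 2a), or apply a stated dilution correction. The like-with-like comparison costs some precision: the standard error is √(0.27 × 2/33) = 0.13 instead of 0.11. Report the sample type of the PIM arm before comparing 11-month values with it.

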### **IgG antibodies**

Blood samples will be transported to the CLB and after centrifugation the serum samples will be stored at -80°C. Later, the samples will be tested for all 13 vaccine pneumococcal polysaccharides and DTaP-Hib using the X-map Luminex technology. Only 100 µl of blood is needed for these analyses.

### **Preparation of PBMCs**

Specific B cell frequencies will be measured for five to six serotypes.

In the previous KOKKI study the following serotypes were tested: 6B, 14, 19F and 23F. They are present in PCV7, PCV10 and PCV13.

For the current study a selection of the 13 serotypes will be made. Probably 6B and 19F from PCV7, one-two serotypes from the three serotypes added by PCV10, and two serotypes added by PCV13 (probably 6A and 19A). The final selection will be based on the carrier frequencies just before evaluation.

Fresh Peripheral Blood Mononuclear Cells (PBMCs) will be separated from heparinized blood, within 24 hours after collection, by density gradient gel centrifugation in CPT tubes (Becton Dickinson). Cells are washed using PBS + 5% fetal calf serum (FCS; HyClone).

PBMC's were resuspended in AIM-V medium containing 10% FCS and supplemented with penicillin (100 U/ml), streptomycin (100 µg/ml) and L-glutamine (200nM) (Gibco BRL).

**B cell stimulation in vitro (memory B cells)**

For the indirect ELISPOT, PBMCs will be resuspended and cultured at a concentration of  $2 \times 10^6$  cells/ml in AIM-V culture medium in 24-wells plates. PBMCs will be stimulated polyclonally with 3 µg/ml CpG-C, PTO modified (5'-TCG TCG TCG TTC GAA CGA CGT TGA T-3') (Isogen) in the presence of 10 ng/ml IL-2 (strathmann), 10 ng/ml IL-10 (Calbiochem) and 2 ng/ml of pooled polysaccharides (Stathens Serum Institute) for 5 days at 37°C and 5% CO2. Cells will be harvested by centrifugation, washed with culture medium and tested in antigen-specific ELISPOT assays.

**Plasma B cells**

To determine plasma cell frequencies, PBMCs are diluted in culture medium to a concentration of  $3 \times 10^6$  cells/ml and used in an ELISPOT to examine the number of plasma cells.

**ELISPOT assay**

Multiscreen Filtration plates were pre-incubated with 35% ethanol for 1 minute, washed and coated with 100 µl PBS containing either 10 µg/ml goat-anti human IgG (SBA), 25 µg/ml used polysaccharide types or PBS only as a negative control. All plates were incubated at 4°C overnight, washed and blocked for at least 20 minutes with PBS containing 5% FCS. Afterwards 3-fold dilutions of the PBMCs suspension (Direct ELISPOT, plasma B cells) were added to the plates at a starting concentration of at least  $3 \times 10^5$  cells/well, or stimulated PBMCs (Indirect ELISPOT, memory B cells) at a starting concentration of at least  $0.5 \times 10^5$  cells/well up to  $2 \times 10^5$  cells/well in AIM-V culture medium and incubated overnight at 37°C and 5% CO2. After washing with 0.05% Tween 20/PBS, plates were incubated with alkaline phosphatase (AP)-labeled goat-anti human IgG (1:5000) (SBA) for 2-4 hrs at 37°C. After washes (last wash in PBS), plates were incubated with 50 µl substrate solution (1 mM 5-bromo-4-chloro-3-indolyl phosphate in H2O; Sigma) for 30-60 minutes. Reaction was stopped by washing and dried. Plaques appearing as blue spots were measured as antigen-secreting cells by using an ELISPOT reader and software (CTL Europe).

**7.4 Withdrawal of individual subjects**

Subjects can leave the study at any time for any reason if they wish to do so without any consequences. The investigator can decide to withdraw a subject from the study for urgent medical reasons.

### **7.5 Replacement of individual subjects after withdrawal**

For sub groups 1a, 1b, 2a and 2b, 33 subjects are collected per sub group (in order to reach 25 evaluable subjects for cellular immunity. The numbers will also enable sufficient samples for antibody concentrations).

Only in case of dropout subject can be replaced:

- Due to the vaccinations of group 1 it is impossible to replace these subjects after all two months vaccinations are given
- In case of being still feasible, subjects in group 2 can be replaced in case subjects drop out during the first visits.

### **7.6 Follow-up of subjects withdrawn from treatment**

Follow-up is only applicable to group 1. When withdrawing before the end of the vaccination schedule, options need to be discussed to make sure that the child receives the necessary vaccinations. A schedule started with PCV13 should be finished with either PCV13 or PCV7 (not by PCV10). Completion of the schedule can be done by the study team, who can give PCV13. If the parents refuse home visits from the study team the well-baby clinic can complete the schedule with PCV7 (since PCV13 is not part of the RVP and the well-baby clinic can therefore not provide PCV13).

### **7.7 Premature termination of the study**

The sponsor is entitled to terminate the study at any time if new data on the safety or efficacy of the product under study becomes available during the study, making further use of the product undesirable, even in a controlled situation. The METC will be informed about such a decision.

The study can be discontinued:

- If the investigator of that site comes into a situation that impedes the further progress of the study and the investigator cannot be replaced or no other solution can be found.
- In case of repeated unacceptable protocol violations.

In case of premature study termination, options should be discussed to ensure complete vaccination series for the children, see chapter 7.6.

## 8. SAFETY REPORTING

### 8.1 Section 10 WMO event

In accordance to section 10, subsection 1, of the WMO, the investigator will inform the subjects and the reviewing accredited METC if anything occurs, on the basis of which it appears that the disadvantages of participation may be significantly greater than was foreseen in the research proposal. The study will be suspended pending further review by the accredited METC, except insofar as suspension would jeopardise the subjects' health. The investigator will take care that all subjects are kept informed.

### 8.2 Adverse and serious adverse events

Adverse events are defined as any undesirable experience occurring to a subject during the study, whether or not considered related to [the investigational product / the experimental treatment]. All adverse events reported spontaneously by the subject or observed by the investigator or his staff will be recorded.

A serious adverse event is any untoward medical occurrence or effect that at any dose:

- results in death;
- is life threatening (at the time of the event);
- requires hospitalisation or prolongation of existing inpatients' hospitalisation;
- results in persistent or significant disability or incapacity;
- is a congenital anomaly or birth defect;
- is a new event of the trial likely to affect the safety of the subjects, such as an unexpected outcome of an adverse reaction, lack of efficacy of an IMP used for the treatment of a life threatening disease, major safety finding from a newly completed animal study, etc.

All SAEs will be reported through the web portal *ToetsingOnline* to the accredited METC that approved the protocol, within 15 days after the sponsor has first knowledge of the serious adverse reactions.

SAEs that result in death or are life threatening should be reported expedited. The expedited reporting will occur not later than 7 days after the responsible investigator has first knowledge of the adverse reaction. This is for a preliminary report with another 8 days for completion of the report.

SAE's and SUSARs will be reported to the CCMO according to the following:

- 1 Group 1: Report all SUSARs within 7 days during the entire trial

- 2 All SAE's related to PCV13 and DTaP-IPV-Hib-HepB vaccination (Group 1) or trial related actions (e.g. venapuncture, all groups) will be reported within 7 (resulting in death or is life threatening) or 15 days (all other) during the entire trial
- 3 Group 1: All SAE's related to invasive pneumococcal disease (IPD) will be reported within 7 (resulting in death or is life threatening) or 15 days (all other) during the entire trial
- 4 Group 1: All unrelated SAEs resulting in death/persistent serious side effects will be reported within 7 days during the entire trial
- 5 All other unrelated SAEs will be reported semiannual
  - a. Group 2: Registration will taken place during one week after blood collection
  - b. Group 1:
    - i. Registration will take place in the period of trial entry until one month after the primary series (in practice until ~5 months of age)
    - ii. During the period of pre-booster blood collection until one month after the booster vaccination
  - c. The report will contain the following: subject number, vaccination date, SAE start and stop date, diagnosis, severity, relation to vaccination or study procedure

